## 1.2 PLATELET GLYCOPROTEIN VI (GPVI)

GPVI is a platelet membrane glycoprotein involved in the formation, growth and stability of thrombi. GPVI belongs to the immunoglobulin receptor family, signaling via the FcR $\gamma$  chain immune tyrosine-based activation motif (ITAM) cascade that includes Bruton tyrosine kinase (Btk). An important point is that GPVI is not strictly required for physiological hemostasis since its deficiency or pharmacological blockade does not provoke significant bleeding (*Jandrot-Perrus M. et al. Platelets 2019; 30:708; Nurden AT. Blood Reviews 2019; 38:100592*). Further, GPVI is exclusively expressed in platelets and their precursors, megakaryocytes. GPVI is therefore generally considered to be a promising target for the treatment of thrombosis (*Mackman et al Nat Rev Drug Discover 2020 March 4*). Besides its role in thrombosis, GPVI is involved in platelet-monocyte interactions (*Schulz C. et al. J Thromb Haemost. 2011;9(5):1007*) and has been reported to play a critical role in the thrombo-inflammation associated with ischemia-reperfusion (*Rayes J. et al J.Clin.Invest. 2019;129:12*). GPVI blockade reduces the inflammatory response after cerebral reperfusion, possibly by limiting the release of IL-1 $\beta$  and polyphosphates and by attenuating inflammatory cell recruitment (*Nieswandt B et al. J Physiol (Lond). 2011;5894115; Nieswandt B et al. J Thromb Haemost. 2011;9(Suppl 1):92*). Similarly, GPVI blockade causes a reduction in inflammatory cell recruitment and infarct size following myocardial ischemia-reperfusion injury (*Pachel C. et al. Arterioscler Thromb Vasc Biol. 2016;36(4):629*). GPVI has also been identified as a player in platelet interactions with pathogens. For example, staphylococcal superantigen-like 5 induces platelet activation via a mechanism involving GPIb and GPVI (*Hu H. et al Plos One 2011*). In terms of viruses, hepatitis C virus interacts with human platelets in vivo and native viral particles have been found to bind to the extracellular domain of GPVI (*Zahn A. et al J Gene Virol 2006*).

**Overall, GPVI could therefore be considered as a valuable candidate target to limit the contribution of platelets to uncontrolled lung inflammation without inducing unwanted bleeding.**

## 2. GLENZOCIMAB (ACT017)

Glenzocimab (ACT017) is a fully humanized anti human GPVI fragment of antibody (Fab) (*Lebozec K et al. N Biotechnol 2018*). Glenzocimab blocks GPVI-triggered platelet activation in vitro. Intravenous administration of glenzocimab is antithrombotic in animal models without inducing bleeding (*Lebozec K et al. Mabs 2017*). In a placebo-controlled phase 1 clinical trial in 48 healthy subjects, glenzocimab administered via a 6-hr infusion at escalating doses up to 2 g proved to be safe and well tolerated, with no SAE being reported, no dose or time-related adverse event, and no bleeding-time prolongation. Its pharmacokinetic/pharmacodynamic properties have been characterized (*Voors-Pette et al. Arterioscler Thromb Vasc Biol 2019;39:956*). Glenzocimab is currently being tested in a double-blind phase 2a clinical trial (ACTIMIS NCT 038030037) in patients with a severe acute ischemic stroke on top of the standard of care. Patients are randomly assigned to a placebo or to glenzocimab (125 up to 1000 mg), administered as a 6-hour infusion. This initial escalating dose phase is in progress, and 37 patients have already been enrolled. No specific safety signal has been reported, while the dose of 1000mg has just been reached. A Data

Safety Monitoring Board adjudicates each new patient cohort, and, so far, after 3 scheduled meetings, no specific warning was issued.

COVID-related ARDS represents another disease condition wherein both micro and sometimes macro-thrombotic events are observed together with inflammation, and therefore a potential new, and complementary indication for glenzocimab, consistent with its mode of action.

However, by contrast with acute ischemic stroke where a decisive therapeutic action is required in a matter of hours, a more prolonged pharmacologic activity may be required in ARDS that entails a rapidly progressing process. It therefore requires a different pattern of administration for glenzocimab, so as to cover a minimum of 3 days, though, admittedly this choice is an arbitrary one, in the absence of any precise indicator of when the platelet activation cascade takes place in the pathogenic process.

PK-PD modeling based on pre-existing glenzocimab PK and PD data, has shown that a constant infusion rate of  $167 \text{ mg h}^{-1}$  for 6 consecutive hours allows for 90% of patients having a  $\geq 80\%$  inhibition of collagen-induced platelet activation for 16 to 18 hrs, a threshold that is arbitrarily admitted as being representative of a full pharmacological effect for GPVI receptor inhibition. Repeating the administration at 24hr-intervals provides the assurance that there would not be any product accumulation in the blood.

## **2.1 RATIONALE**

## **2.2 PHARMACOLOGY**

In vitro, glenzocimab dose-dependently inhibited collagen-induced platelet aggregation with a full inhibition for concentration  $\geq 5 \text{ } \mu\text{g/mL}$ . In transgenic mice model expressing the hGPVI, glenzocimab showed a dose-dependent inhibition of the ex-vivo aggregation induced by collagen ( $1 \text{ } \mu\text{g/mL}$  of collagen) on concentrated platelet rich plasma (cPRP). Administration of glenzocimab did not modify either the platelet count or induced any modification in hGPVI expression. In cynomolgus monkeys, the minimum effective dose (MED) is  $2 \text{ mg/kg}$ . Glenzocimab administered as a 15-min injection at  $2$  to  $8 \text{ mg/kg}$  doses fully inhibited collagen-induced platelet aggregation  $0.5$  hrs after the end of the administration. Neither the platelet count nor bleeding time were modified. Slow administration of glenzocimab (1- hr infusion) at  $8 \text{ mg/kg}$  resulted in a prolonged inhibition of collagen-induced platelet aggregation lasting for  $7$  hrs, with a total inhibition for all animals lasting  $2$  hrs. A 6-hr infusion of glenzocimab administered at  $8 \text{ mg/kg}$ , with  $\frac{1}{4}$  of the dose administered in  $15$  min and  $\frac{3}{4}$  of the dose administered in  $5$  hrs  $45$  min, resulted in a profound inhibition of collagen-induced platelet aggregation lasting  $9$  hrs. At  $24$  hrs, the effect of glenzocimab was fully reversed for  $3$  of the  $4$  animals.

A model of platelet-dependent intravascular thrombosis induced by a collagen/adrenaline mixture was developed in hGPVI transgenic mice. At  $8 \text{ mg/kg}$ , glenzocimab has been shown to protect animals from thrombosis.

Co-administration of glenzocimab (8 mg/kg, 6-hr infusion) and tPA (1 mg/kg, 1-hr infusion) in cynomolgus monkeys showed neither impact on rtPA activity nor on its PK profile, as well as no impact on glenzocimab activity on platelet aggregation induced by collagen and no impact on glenzocimab PK profile. ADP-induced platelet aggregation was also not modified either by the co-administration.

In a photochemically-induced thrombotic stroke model in cynomolgus monkeys, administration of glenzocimab (8 mg/kg) resulted in no increase of intracerebral hemorrhage rate and volume. It also showed a trend in favor of a reduced infarct size.

### 2.2.1 Safety Pharmacology

A study of the safety pharmacology was conducted to evaluate the effect of glenzocimab on the CNS, respiratory and cardiovascular functions. This study was integrated in the pivotal toxicology study (ACT-NCS-002) conducted on Cynomolgus monkeys.

At all doses assessed (8, 25 and 80 mg/kg), glenzocimab had no effects on the CNS (according to the functional observation battery), and on the cardiovascular and respiratory function (assessed with a jacketed external telemetry).

### 2.2.2 Toxicology

Safety and toxicity of glenzocimab were assessed in two toxicology studies ACT-NCS-001 (ACT-NCS-001 2016) and ACT-NCS-002 (ACT-NCS-002 2017) after a single 6-hr infusion in cynomolgus monkeys. The target pharmacological dose of 8 mg/kg was tested as well as a high dose of 80 mg/kg and an intermediate dose of 25 mg/kg.

No signs of systemic toxicity or bleeding were observed at dose-levels of 8, 25 or 80 mg/kg. Local reactions at the injection site were observed in some animals, mainly on the day following the i.v. infusion and without dose-relationship. Body weight and food consumption were not affected by the treatment. Changes observed in hematological parameters (decreases in red blood cell count, hemoglobin concentration and packed cell volume) were attributed to the several blood samplings collected over a 48-hr period. At blood biochemistry, increases in creatine kinase and lactate dehydrogenase activity observed in almost all control and test item-treated animals were considered to be likely associated with muscle damage caused by the contention in restraint chairs for an extended period of time.

A tissue cross reactivity (TCR) study (ACT-NCS-003) was performed to confirm that glenzocimab does not bind to extra target sites. GPVI expression is limited to platelets and megakaryocytes and therefore no binding to tissues was expected. A panel of 42 tissues and blood smears from 3 unrelated human donors was screened. Binding was observed in blood smears, spleen (red pulp) and bone marrow, which is consistent with platelets and/or megakaryocytes sites. No staining was observed with other tissues. In an *in vitro* hemolysis study conducted with human blood samples, glenzocimab showed no hemolytic potential.

In summary, the results of the toxicity studies in Cynomolgus monkeys have not revealed any potential toxicities that would preclude the use of glenzocimab in a healthy subject. It was well tolerated at doses up to 80 mg/kg. Consequently, a no observed adverse effect level (NOAEL) of 80 mg/kg was extrapolated.

### 2.2.3 Metabolism in Animals

A dedicated biodistribution study was also conducted in hGPVI transgenic mice using radiolabeled glenzocimab with Iodine-125 to determine its blood, plasma and tissue distribution. Results showed a fast clearance from blood circulation as 98% of the injected dose was eliminated after 3 hrs. The analyzed data tended to confirm a specific binding of glenzocimab to platelets. Activities measured in organs and tissues did not reveal unexpected exposure of the drug and clearly identified that renal elimination was the main route of elimination (it contributed for about 99% of the elimination process), which was consistent with the elimination of a Fab fragment of 48 kDa. A moderate splenic sequestration (less than 3% ID/g) of radiolabeled glenzocimab was highlighted probably due to the presence of platelets. Finally, there was no bone marrow sequestration of the radiolabeled drug, though it could have been expected as bone marrow is the production site for platelets.

In Cynomolgus monkeys, the PK profiles following a 6-hr i.v. infusion in two successive phases (a 15-min loading dose phase of  $\frac{1}{4}$  of the total dose and a maintenance dose phase of  $\frac{3}{4}$  of the total dose), yielded a rapid steady state starting between the first and the third hour after the beginning of the infusion and maintained throughout all of it.

No consistent sex-related differences were reported in Cynomolgus monkeys and the linearity of concentration increments was demonstrated within the dose range of 8 mg/kg to 80 mg/kg. There was no dose-dependency of the total clearance.

An elimination half-life ( $t_{1/2}$ ) of around 9.4 hrs and an average total clearance (Clt) of about 90 mL/h/kg were estimated for glenzocimab in Cynomolgus monkeys. At the higher dose level tested (80 mg/kg), considered to be the No Observed Adverse Effect Level (NOAEL), the mean exposure values (males/females), namely Cmax and AUC0-∞ were determined at 316/263 µg/mL and 989/928 h.µg/mL.

A pharmacokinetic/pharmacodynamics (PK/PD) analysis showed that the estimated 50% inhibitory concentration (IC50) was 0.72 µg/mL (95%CI: 0.47-0.99), confirming the strong potency of glenzocimab to inhibit platelet aggregation in cynomolgus monkeys at the target pharmacological dose.

### 2.2.4 Preliminary Clinical Experience: FIH Healthy Subjects Relevant Results

A preliminary FIH study was conducted in healthy subjects from October 30th 2017 through January 2018. The study was designed as a single-center, randomized, double blind, placebo-controlled, single ascending-dose escalation trial. Healthy subjects received either glenzocimab or a placebo as an 6-hr IV infusion, with a 15-min loading dose representing  $\frac{1}{4}$  of the total dose and a maintenance dose phase of 5hrs and 45 min representing the remaining  $\frac{3}{4}$  of the total dose. Total doses of 62.5, 125, 250, 500, 1000, 2000 mg, and a matching placebo were administered. Safety, clinical tolerability, biological safety as well as PK were the outcome parameters. Ex-vivo collagen-induced platelet inhibition as the main pharmacodynamic (PD) parameter was also tested at serial time points.

There were no Serious Adverse Event reported at any of the doses tested, nor was there any dose- or time-related trend in any non-serious adverse effect (AEs). None of the AEs were identified as bleeding related and neither modifications of the hemostatic parameters nor of hemoglobin

concentration were observed. Bleeding time was not affected in a clinically significant manner by any of the glenzocimab doses. The detailed description of all adverse events reported can be found in the Investigator's Brochure.

Results showed that glenzocimab dose-dependently inhibited collagen-induced platelet aggregation. At the dose of 62.5 mg, collagen-induced platelet aggregation was observed in 3 out of 6 subjects, and results returned to baseline 1 hr after dosing. At the dose of 125 mg, platelet aggregation was rapidly inhibited in 4 out of 6 subjects and the effect lasted 6 hrs. At 250 mg, the inhibition was more homogeneous across the subjects (inhibition observed in 5 out of 6 subjects) with an effect lasting around 6 hrs. At the doses of 500 mg, 1000 mg and 2000 mg, the inhibition was observed in all subjects, with an effect lasting around 8 hrs, 18 hrs and 24 hrs, respectively. At 48 hrs, platelets aggregation returned to baseline levels at all dose levels, except for the 2000 mg, for which return to baseline levels was observed at follow-up (Day 7).

For all doses investigated, the applied dosing regimen indeed showed a fast increase in glenzocimab plasma concentrations within the first 15 min of administration. Thereafter, the speed of infusion was reduced, resulting in more or less stable plasma concentrations for the remaining infusion time. Total clearance was constant for all doses. The primary PK parameters  $C_{max}$  and AUC, demonstrated dose proportionality across the investigated dose range. Recovery of glenzocimab in urine is only significant (> 1%) at the two highest doses.

These preliminary data concur with those observed in non-human primates.

### **2.2.5 Ongoing First-in-patient Clinical Trial: ACTIMIS Study**

The first-in-patient study in acute stroke combines a phase Ib dose escalation of glenzocimab as add-on therapy to the best standard of care (rtPA +/- thrombectomy) to assess the safety and to identify the recommended phase 2 dose (RP2D), and a phase 2a dose-expansion in order to confirm the safety of the RP2D and to assess glenzocimab potential activity on AIS assessment parameters. Due to its specific mechanism of action showing no evidence of any additional bleeding risk both in animals or in healthy subjects, glenzocimab candidate drug seems to be a promising agent administrable at the acute phase of the stroke in addition to the best standard of care with the following medical management objectives:

- 1) Reduce the size of the clot,
- 2) Favor cerebral reperfusion, thus decreasing the infarct volume

Decrease the occurrence of ischemia-reperfusion injury, thereby increasing the percentage of salvageable brain tissue and improving neurological recovery.

### **2.2.6 Rationale of the Study**

To offer an additional treatment option for SARS-CoV-2 infected patients who present with acute respiratory distress syndrome. This treatment might also prevent downstream complications due to pro-thrombotic conditions. If positive, other viral sepsis conditions could benefit from this exploratory approach.

### 2.2.7 Study Dose Selection

In the ongoing phase 1b/2a clinical trial (ACTIMIS; NCT 038030037) in acute ischemic stroke, glenzocimab is administered in a single 6h infusion with  $\frac{1}{4}$  of the dose administered in a 15-minute bolus injection and the rest of the dose in 5h45.

In the proposed GARDEN study, by contrast with acute ischemic stroke where a decisive therapeutic action is required in a matter of hours, a more prolonged pharmacologic activity may be required in ARDS that entails a rapidly progressing process. It therefore requires a different pattern of administration for glenzocimab, so as to cover a minimum of 3 days, though, admittedly this choice is an arbitrary one, in the absence of any precise indicator of when the platelet activation cascade takes place in the pathogenic process.

The proposed administration is 1000 mg over 6 hours without bolus injection at D1, D2 and D3. This is based on the below PK-PD modeling.

#### ➤ PK-PD modeling

PK-PD modeling based on pre-existing glenzocimab PK and PD data, has shown that a constant 1000 mg infused for 6 consecutive hours allows 90% of patients having a  $\geq 80\%$  inhibition of collagen-induced platelet activation for 16 to 18 hrs, (see graph below), a threshold that is arbitrarily admitted as being representative of a full GPVI receptor pharmacological inhibition.

[figure not shown]

**Figure 1: PK/PD model was built on glenzocimab (ACT017) plasma concentration and ex vivo platelet aggregation data from a phase I study in healthy volunteers (median concentration-time profiles by dose overlaid on individual observations - ACT017 LLOQ = 0.3  $\mu\text{g/mL}$ ).**

From a PK standpoint, glenzocimab concentrations (PK) were determined in the 48-subject escalating dose, phase 1 study in each individual receiving glenzocimab (n=36 subjects), both pre-dose and then 15 minutes, 1, 4, 6, 8, 10, 14, 18, 24 and 48 hours after the start of the infusion. Glenzocimab concentrations in all individuals were also determined at  $144 \pm 48$  hours after the start of infusion. A total of 390 PK observations were included in the PK analysis.

Glenzocimab was found to have dose-proportional, two-compartmental PK with a central distribution volume of 4.1 L, and first and second half-lives of 0.84 and 9.6 hours (see graph below).

[figure not shown]

**Figure 2: PK/PD model was built on glenzocimab (ACT017) plasma concentration and ex vivo platelet aggregation data from a phase I study in healthy volunteers** (median concentration-time profiles by dose overlaid on individual observations - ACT017 LLOQ = 0.3 µg/mL).

On the basis of these preliminary data, a dose of 1000mg infused constantly over a 6-hr period at a constant infusion rate of 167 mg/hr every 24 hrs for 3 days was selected for the proposed GARDEN study.

PK simulation (see graph below), upon readministration of 1000mg at 24hr interval, following a 6-hr infusion, shows that less than 1% of the drug can be found in the plasma, making accumulation totally unlikely. Cmax values remain similar over the 3-day period of administration. Based on this, each administration should be regarded as a 'single' new administration in the same patient.

[figure not shown]

**Figure 3: 166.67 mg/h as 6-h IV infusion q1day for 3 days (total dose of 3'000 mg): Predicted plasma glenzocimab (ACT017) concentration** (1'000 simulations. Line = median, shaded area = 10th to 90th percentile).

With this pattern of administration, 90% of subjects should have an inhibition of platelet activation between 50 and 95% for the 3-day period of treatment.

[figure not shown]

**Figure 4: 166.67 mg/h as 6-h IV infusion q1day for 3 days (total dose of 3'000 mg): Predicted inhibition of collagen-induced platelet aggregation (1'000 simulations. Line = median, shaded area = 10th to 90th percentile).**

#### ➤ Safety data from previous tested doses

In healthy volunteers, the maximum administered dose was 2000mg over 6 hrs by IV infusion. No dose or time-related adverse event, and no bleeding event, even minor, was reported at any of the dose tested, and the 2000mg dose was considered, by default as the maximum tolerated dose. No higher dose was tested as 2000mg was considered to be 2 to 4 times superior to the target active pharmacological dose.

In acute ischemic stroke patients, the maximum tested dose is currently 1000mg infused over 6hrs with ¼ of the dose injected as an IV bolus in 15 minutes at the initiation of

the infusion. In this case, 100% of treated patients receive also rtPA as a 0.9mg/kg I-hr infusion, within 4.5 hrs of the onset of stroke symptoms. Glenzocimab infusion initiation should take place less than 1 hr after the end of rtPA infusion, so that both products are present concomitantly in each patient for a period of time varying from 1 to 2 hours. So far the cohort 4 is ongoing, though not all patients have been dosed yet, there has been no specific safety signal attributable to the addition of glenzocimab to rtPA in what regards bleeding events, and no dose-related trend has been noted.

➤ **Immunogenicity**

Regarding immunogenicity, glenzocimab was assessed in silico using the EpiMatrix Protein Immunogenicity Scale from EpiVax. EpiMatrix predicted excess and shortfall in aggregate immunogenicity relative to a random protein standard. All scores are adjusted for the presence of Tregitopes. The submitted glenzocimab sequence scores on the low end of EpiMatrix scale. The combined analysis of glenzocimab heavy and light chains indicates that the immunogenic potential of the antibody is low. As compared to other antibodies, using this established method for calculating immunogenicity, it is estimated that glenzocimab antibody could yield an antitherapeutic response in approximately 2.00% (+/-5%) of exposed subjects.

In healthy volunteers, no dose- or time dependent changes in the immunogenicity ADA data were observed. In the current ACTIMIS study in acute ischemic stroke, no specific safety signal related to the immunogenicity was observed.

➤ **Conclusion**

**Based on the above it is therefore the Applicant's opinion that there should be no rationale requiring additional, repeated dose non clinical and clinical (healthy volunteer) studies to support the repeat administration of glenzocimab at 1000 mg over 6hr infusion every 24hrs.**

### **3. STUDY OBJECTIVES**

#### **3.1 PRIMARY OBJECTIVE**

To evaluate the effect of glenzocimab in preventing clinical progression of disease, when added to Standard-of-Care in Covid-19 patients presenting with a progressive and moderate respiratory distress syndrome.

#### **3.2 SECONDARY OBJECTIVE(S)**

##### **3.2.1 Efficacy:**

- To assess the impact of treatment on overall disease control,
- To assess the impact of treatment on symptomatology and biological parameters.

##### **3.2.2 Safety:**

- To assess the number of the following events:
  - deaths,
  - serious adverse events (SAEs),
  - suspected unexpected serious adverse reactions (SUSARs)
  - medically important events,
  - bleeding-related events.

##### **3.2.3 Pharmacokinetics**

- Confirmation of overall PK profile on single and repeated administration (Days 1, 2 and 3), for comparison with initial PK-PD simulation:
  - baseline
  - Cmax: middle of infusion (3hrs post initiation)
  - elimination phase (3 hrs after the end of infusion)
  - residual plasma level: 24 hrs after first infusion initiation (i.e. 18 hrs after the end of infusion)

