|                     | 
 
To assess the number of the following events: 
 
deaths,
 
serious adverse events (SAEs),
 
suspected unexpected serious adverse reactions (SUSARs),
 
medically important events,
 
bleeding-related events.
 
 
 
 
Pharmacokinetics:
 
 
To verify that actual PK profile in patients does not differ from that in healthy volunteers, and matches with PK-PD simulation.
 
 
Exploratory:
 
 
Evolution of pulmonary lesions on chest imaging,
 
Evolution of biological parameters related to hemostasis, coagulation and inflammation,
 
Determination of predictive factors for a response.
 
                                                                                                                                                                                                                                                                                                                                                                                                                                                                                                                                                                                                     |

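### The 3-hour mid-infusion PK sample is labelled Cmax, but under a constant 6-hour infusion without bolus the modelled peak is at the end of infusion, where no sample is planned (minor)

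*Protocol*

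**What the plan says.** The Synopsis states the PK objective as "To verify that actual PK profile in patients does not differ from that in healthy volunteers", and adds that it should match the PK-PD simulation. Section 3.2.3 lists the sampling points, "for comparison with initial PK-PD simulation", and gives Cmax as the "middle of infusion (3hrs post initiation" sample.

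The regimen is in section 2.2.7: "1000 mg over 6 hours without bolus injection at D1, D2 and D3", restated under PK-PD modeling as "a dose of 1000mg infused constantly over a 6-hr period at a constant infusion rate of 167 mg/hr". The same section describes dose-proportional two-compartment kinetics with a "central distribution volume of 4.1 L" and "first and second half-lives of 0.84 and 9.6 hours". It also says that under 1% of the drug is found in plasma on readministration at 24 hours, and that Cmax is similar on the three days. It gives no numeric Cmax.

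The flowchart (7.1), sections 7.4-7.6, Table 1 in 7.13.2 and section 9.4.1 agree on the draws: before each infusion, 3 h after its start and 3 h after its end, plus one sample 24 h after the start of the third infusion. None falls at the end of infusion. Section 11.5.3 plans description over all time-points and graphs.

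**The concern.** The name and the clock time do not agree. In the healthy-volunteer study (section 2.2.4) a quarter of the dose went in over the first 15 minutes, and concentrations were then roughly stable for the rest of the infusion. A mid-infusion draw represents that plateau. This trial drops the loading phase, so there is no early plateau to sample. The healthy-volunteer study also sampled at 6 h, and this one does not.

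If the 3-h value is tabulated as Cmax and set against a simulated Cmax, patients will appear to peak lower than predicted even when the model is exactly right. The gap is not a fixed offset, because it depends on how fast the patient clears the drug.

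**Working it through.** **Inputs, all from section 2.2.7:** dose 1000 mg over T = 6 h; central volume V = 4.1 L; half-lives 0.84 h and 9.6 h; under 1% in plasma at 24 h. Clearance, or equivalently the weight w of the slow phase in the disposition curve, is not stated, so w is varied.

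**1. The plan's own figure.** R = 1000/6 = 166.67 mg/h. This reproduces the stated 167 mg/h.

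**2. Where the peak lies.** α = ln 2/0.84 = 0.8252/h and β = ln 2/9.6 = 0.0722/h. During the infusion

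C(t) = (R/V)·[(1−w)(1−e^(−αt))/α + w(1−e^(−βt))/β].

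Its slope is (R/V)·[(1−w)e^(−αt) + w·e^(−βt)], which is positive for every w from 0 to 1. The maximum is therefore at 6 h whatever the missing parameter is.

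**3. Size with the protocol's parameters.** R/V = 40.65 mg/L per hour. The fast term (1−e^(−αt))/α is 1.110 at 3 h and 1.203 at 6 h. The slow term is 2.697 and 4.869. The statement about 24 h limits w:
- read as C(24h)/C(6h) < 1%, it gives w ≤ 0.0093;
- read as under 1% of the dose in the central volume, it gives w ≤ 0.045 (at that limit C(24h) is 2.44 mg/L, and 2.44 × 4.1 = 10 mg of 1000 mg).

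| w | C(3h), µg/mL | C(6h), µg/mL | C(3h)/C(6h) | shortfall |
|---|---|---|---|---|
| 0 | 45.1 | 48.9 | 0.922 | 7.8% |
| 0.0093 | 45.7 | 50.3 | 0.909 | 9.1% |
| 0.045 | 48.0 | 55.6 | 0.863 | 13.7% |

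**4. Slower elimination (assumption).** Take k21 = β + w(α−β), k10 = αβ/k21 and k12 = α + β − k21 − k10. Halve k10, hold V, k12 and k21, and recompute the exponents and weight. Each cell shows base → halved, in µg/mL.

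| w | 3 h | 6 h | 9 h | shortfall at 3 h when halved |
|---|---|---|---|---|
| 0 | 45.1 → 70.0 | 48.9 → 90.2 | 4.1 → 26.2 | 22.5% |
| 0.0093 | 45.7 → 68.0 | 50.3 → 87.6 | 5.6 → 26.4 | 22.3% |
| 0.045 | 48.0 → 64.4 | 55.6 → 84.2 | 11.1 → 30.1 | 23.5% |

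The rise is 1.3- to 1.55-fold at 3 h, 1.5- to 1.8-fold at 6 h, and 2.7- to 6.4-fold at 9 h.

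**5. Across days.** Summing C over the three infusions, 24 h apart, the Day 3/Day 1 ratio is 1.00-1.05 at 3 h and 1.00-1.03 at 6 h. With elimination halved it is 1.00-1.14 and 1.00-1.09.

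**6. Sensitivity of an end-of-infusion draw to timing.** After the stop, the fast part decays by e^(−αδ) and the slow part by e^(−βδ). A draw 7 minutes late loses 7.8-9.2% and one 15 minutes late loses 16-19%. By the formula in step 2, a draw 15 minutes before the stop loses less than 1%.

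**The case against.** A reader might infer that the label hides high exposure in patients who clear the drug slowly. The documents do not support that. Step 4 shows that the 3-h value itself rises when elimination is halved, and that the planned 9-h sample rises far more than a 6-h sample would. The pre-dose and 24-h draws add to this, so slow clearance would be seen.

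A reader might also infer that the case for repeat dosing, similar Cmax from day to day, can no longer be checked. That does not follow either. All three days are sampled at the same clock time, and step 5 shows the 3-h draw to be at least as sensitive to accumulation as a 6-h draw.

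The best defence of the text is that only section 3.2.3 uses the word Cmax for this sample. The operative sections name it by clock time, section 7.13.2 requires actual sampling and dosing times, and the simulation yields a whole curve, so 3-h values can be compared like with like. Any Cmax derivation may also be set out in the SAP, which is not at hand. All of this stands, and it limits the consequence. It does not make the label right: section 3.2.3 names a peak, the sample is not at the peak, and no planned draw measures the peak directly.

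Moving the draw also has a real drawback. Section 4.3.1 allows suspensions within a total of 7 hours, and section 6.5 allows pauses and reduced rates, so the stop time can shift. A draw 7 minutes after the stop brings back an error of about the size being removed.

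**Conclusion.** The point holds as a minor error. The sample that section 3.2.3 calls Cmax is not at the modelled peak. It understates the peak by about 8-9% with the protocol's half-lives, by up to about 14% if the statement about 24 h refers to the share of dose in the central volume, and by about 22-23% if elimination is halved.

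The direction follows from constant-rate input and linear kinetics and does not depend on the missing clearance. The sizes depend on the range taken for w, and the last figure also on the assumptions of halved elimination and unchanged distribution. Section 6.5 also mentions a low, gradually increasing infusion rate, which does not agree with the constant rate in 2.2.7. The two passages must be reconciled, and a rising rate would put the 3-h value further from the peak.

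Only the reported peak in a secondary, descriptive objective is affected. Efficacy, sample size and alpha are untouched, and PK results are not among the data that section 4.5 lists for the DSMB.

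**What to change.** In section 3.2.3, rename the sample C3h and compare it with the simulated 3-h concentration. Derive Cmax only from the PK model, using the recorded actual dosing and sampling times. This is a wording change with no effect on sampling.

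If an observed Cmax is wanted, move the on-infusion draw on Days 1-3 to just before the actual end of infusion, and record the exact stop and draw times. Keep the draws 3 h after the end and at 24 h or pre-dose. The number of samples stays the same. The cost is a draw tied to a stop time that can move, with the late-draw loss shown above, and there would no longer be a mid-infusion sample.

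For either option, bring sections 3.2.3, 7.4-7.6 and 9.4.1, the flowchart and Table 1 into line.
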